## **Budget justification**

A total of TSh 902,900.00 is required to facilitate purchase of stationery and payment for secretarial services. The amount will be used to print, photocopy and bind six copies research proposal. It will also facilitate printing and photocopying of consent forms, questionnaires and clinical data collection forms for 1155 participants. Furthermore, the amount will be used to print and bind 8 thesis reports. A total of TSh 7,320,000.00 is budgeted for payment of allowance for dentists and assistants who will work at the field for a total of 90 days each.

Communication and transport of researchers and assistants to and from field sites during baseline data collection, institution of the intervention and follow ups in 4 districts will require a total of TSh 3,047,600.00. Modified basic package of oral health care will involve treatment and therefore TSh 15,509,000.00 is allocated to facilitate purchase of toothpastes and brushes, dental instruments, dental materials and medical supplies. Data entry and analysis will require a total of TSh 700,000 as payment of data entry clerks and statistician. Local and international conference presentations are required as part of dissemination of findings and fulfilment of PhD and therefore TSh 3,100,000.00 is allocated as travel, accommodation and conference attendance fees.

The proposal will require to be ethically cleared by MUHAS research committee and TDRC in Zambia and for that reason TSh 760,000.00 is allocated for ethical clearance. The study will be done in span of 2 years hence 10% of the budget (TSh 3,121,950.00) is set aside to compensate for inflation and other unforeseen costs. In conclusion a total budget of **TSh 34,341,450.00** is required to facilitate completion of the research project.

## 6.0 Activity Plan

| Activity                                            |            | Implementation plan |     |     |             |      |     |     |     |     |     |     |             |      |     |     |            |     |     |            |             |             |              |             |             |             |  |
|-----------------------------------------------------|------------|---------------------|-----|-----|-------------|------|-----|-----|-----|-----|-----|-----|-------------|------|-----|-----|------------|-----|-----|------------|-------------|-------------|--------------|-------------|-------------|-------------|--|
|                                                     |            | 2020                |     |     |             | 2021 |     |     |     |     |     |     |             | 2022 |     |     |            |     |     |            | 2023        |             |              |             | 2024        |             |  |
|                                                     | Feb
Jun | Jun
sep          | Nov | Dec | Jan-
Mar | Apr  | May | Jun | Jul | Aug | Sep | Oct | Nov-
Dec | Jan  | Feb | Mar | Apr
Jun | Jul | Aug | Sep
Dec | Jan-
Mar | Apr-
Jun | July
Sept | Oct-
Dec | Jan-
Mar | Apr-
Jun |  |
| Preparation of Research Proposal                    |            |                     |     |     |             |      |     |     |     |     |     |     |             |      |     |     |            |     |     |            |             |             |              |             |             |             |  |
| Ethical approval Tanzania & Zambia                  |            |                     |     |     |             |      |     |     |     |     |     |     |             |      |     |     |            |     |     |            |             |             |              |             |             |             |  |
| Training, calibration & questionnaire pretesting    |            |                     |     |     |             |      |     |     |     |     |     |     |             |      |     |     |            |     |     |            |             |             |              |             |             |             |  |
| Base line data collection & intervention            |            |                     |     |     |             |      |     |     |     |     |     |     |             |      |     |     |            |     |     |            |             |             |              |             |             |             |  |
| Attend courses MUHAS                                |            |                     |     |     |             |      |     |     |     |     |     |     |             |      |     |     |            |     |     |            |             |             |              |             |             |             |  |
| Data entry, cleaning & analysis                     |            |                     |     |     |             |      |     |     |     |     |     |     |             |      |     |     |            |     |     |            |             |             |              |             |             |             |  |
| Preparation of 1 st manuscript           |            |                     |     |     |             |      |     |     |     |     |     |     |             |      |     |     |            |     |     |            |             |             |              |             |             |             |  |
| Submission of 1 st manuscript to journal |            |                     |     |     |             |      |     |     |     |     |     |     |             |      |     |     |            |     |     |            |             |             |              |             |             |             |  |
| 1 st follow up data collection (6month)  |            |                     |     |     |             |      |     |     |     |     |     |     |             |      |     |     |            |     |     |            |             |             |              |             |             |             |  |
| Data entry, cleaning & analysis                     |            |                     |     |     |             |      |     |     |     |     |     |     |             |      |     |     |            |     |     |            |             |             |              |             |             |             |  |
| 2 nd manuscript preparation              |            |                     |     |     |             |      |     |     |     |     |     |     |             |      |     |     |            |     |     |            |             |             |              |             |             |             |  |
| Attending courses at University of Bergen           |            |                     |     |     |             |      |     |     |     |     |     |     |             |      |     |     |            |     |     |            |             |             |              |             |             |             |  |
| Submission of 2 nd manuscript to journal |            |                     |     |     |             |      |     |     |     |     |     |     |             |      |     |     |            |     |     |            |             |             |              |             |             |             |  |

| Activity                                            | Implementation plan |     |     |         |     |     |     |     |     |     |     |         |      |     |     |     |         |     |         |         |         |           |         |         |         |  |
|-----------------------------------------------------|---------------------|-----|-----|---------|-----|-----|-----|-----|-----|-----|-----|---------|------|-----|-----|-----|---------|-----|---------|---------|---------|-----------|---------|---------|---------|--|
|                                                     | 2020                |     |     | 2021    |     |     |     |     |     |     |     |         | 2022 |     |     |     |         |     |         | 2023    |         |           |         | 2024    |         |  |
|                                                     | Oct                 | Nov | Dec | Jan-Mar | Apr | May | Jun | Jul | Aug | Sep | Oct | Nov-Dec | Jan  | Feb | Mar | Apr | Jun-Jul | Aug | Sep-Dec | Jan-Mar | Apr-Jun | July-Sept | Oct-Dec | Jan-Mar | Apr-Jun |  |
| Data entry, cleaning & analysis                     |                     |     |     |         |     |     |     |     |     |     |     |         |      |     |     |     |         |     |         |         |         |           |         |         |         |  |
| 3 rd manuscript preparation              |                     |     |     |         |     |     |     |     |     |     |     |         |      |     |     |     |         |     |         |         |         |           |         |         |         |  |
| Submission of 3 rd manuscript to journal |                     |     |     |         |     |     |     |     |     |     |     |         |      |     |     |     |         |     |         |         |         |           |         |         |         |  |
| 3 rd follow up data collection (18month) |                     |     |     |         |     |     |     |     |     |     |     |         |      |     |     |     |         |     |         |         |         |           |         |         |         |  |
| Data entry, cleaning & analysis                     |                     |     |     |         |     |     |     |     |     |     |     |         |      |     |     |     |         |     |         |         |         |           |         |         |         |  |
| 3 rd Presentation at conferences         |                     |     |     |         |     |     |     |     |     |     |     |         |      |     |     |     |         |     |         |         |         |           |         |         |         |  |
| Writing Thesis                                      |                     |     |     |         |     |     |     |     |     |     |     |         |      |     |     |     |         |     |         |         |         |           |         |         |         |  |
| 4 th follow up data collection (24month) |                     |     |     |         |     |     |     |     |     |     |     |         |      |     |     |     |         |     |         |         |         |           |         |         |         |  |
| Data entry, cleaning & analysis                     |                     |     |     |         |     |     |     |     |     |     |     |         |      |     |     |     |         |     |         |         |         |           |         |         |         |  |
| 4 th manuscript preparation              |                     |     |     |         |     |     |     |     |     |     |     |         |      |     |     |     |         |     |         |         |         |           |         |         |         |  |
| 4 th Presentation at conferences         |                     |     |     |         |     |     |     |     |     |     |     |         |      |     |     |     |         |     |         |         |         |           |         |         |         |  |
| Submission of 4 th manuscript to journal |                     |     |     |         |     |     |     |     |     |     |     |         |      |     |     |     |         |     |         |         |         |           |         |         |         |  |
| Submission of thesis                                |                     |     |     |         |     |     |     |     |     |     |     |         |      |     |     |     |         |     |         |         |         |           |         |         |         |  |

## 8.0 Appendices

### Appendix 1 Adolescents 'English Questionnaire

Adolescents ID No

|  |  |  |  |
|--|--|--|--|
|  |  |  |  |
|--|--|--|--|

## EFFECTIVENESS OF MODIFIED BASIC PACKAGE OF ORAL CARE ON ORAL HEALTH STATUS AND RELATED QUALITY OF LIFE AMONG ZAMBIAN ADOLESCENTS-: A FIELD TRIAL

### Instructions

This questionnaire has a three (3) parts with a total of thirty-nine (39) questions. Answer all questions by ticking in inside the box corresponding to answer of your choice. Some questions may have more than one answer.

### Part 1 Demographic information of adolescent and parents/ guardians

1. What is your sex?

1 Male ☐

2 Female ☐

2. What is your birth date?

|                      |                      |                      |                      |                      |                      |
|----------------------|----------------------|----------------------|----------------------|----------------------|----------------------|
|  |  |  |  |  |  |
| DD                   |                      | MM                   |                      | YY                   |                      |

3. Where do you live?

Ward .....

Disrtict .....

4 Do you live with both parents at home?

1. Yes

2. No, Mother only

3. No, Father only

4. No, I live with guardian

5. Others

|  |
|--|
|  |
|  |
|  |
|  |

Specify.....

5 What is the highest education level of your father?

1. No formal education

2. Primary education

3. Secondary education

4. College/University

5. I don't know

6. Not applicable

|  |
|--|
|  |
|  |
|  |
|  |
|  |
|  |

6 What is the highest education level of your mother?

|    |                     |                          |
|----|---------------------|--------------------------|
| 1. | No formal education |  |
| 2. | Primary education   |  |
| 3. | Secondary education |  |
| 4. | College/University  |  |
| 5. | I don't know        |  |
| 6. | Not applicable      |  |

7 How many members make your family (including your parents /guardians, yourself, your brothers and sisters and other people permanently living at your home (excluding visitors) .....

8 How many children are living and taken care of by your parents/ guardians (including yourself, your brothers and sisters and other children 19 years or younger (excluding visitors) living at your home .....

9 Do you have the following at your house? (You can tick more than 1)

| Items |              | Yes                      | No                       |
|-------|--------------|--------------------------|--------------------------|
| 1     | Television   |  |  |
| 2.    | Refrigerator |  |  |
| 3.    | Phone        |  |  |
| 4.    | Car          |  |  |
| 5     | Motorcycle   |  |  |
| 5.    | Bicycle      |  |  |

10 How many sleeping rooms do the house you live in has?

| Items |               |                          |
|-------|---------------|--------------------------|
| 1     | Zero to One   |  |
| 2.    | Two           |  |
| 3     | Three or more |  |

11 Which of the following describe the floor of your house?

| Items |                                               |                          |
|-------|-----------------------------------------------|--------------------------|
| 1     | None , mud or dung                            |  |
| 2.    | Cemented/ concrete/ raw wood                  |  |
| 3.    | Finished floor with carpet , tiles or ceramic |  |

12 Do you have any of the following at home?

|                    | Yes                      | No                       |
|--------------------|--------------------------|--------------------------|
| 1. Dish washer     |  |  |
| 2. Dish dryer      |  |  |
| 3. Computer        |  |  |
| 4. Motor boat      |  |  |
| 5. Air conditioner |  |  |
| 6. Generator       |  |  |

13 Which of the following describe a toilet at your home?

Items

|    |                                          |                          |
|----|------------------------------------------|--------------------------|
| 1  | Traditional pit latrine toilet/no toilet |  |
| 2. | Public toilet/Improved pit latrine       |  |
| 3  | Private Flash toilet                     |  |

14 Where do you get water at your home?

Items

|    |                                                        |                          |
|----|--------------------------------------------------------|--------------------------|
| 1  | Unprotected well, bore hole shallow well surface water |  |
| 2. | Public tap, protected well, tanker track               |  |
| 3  | Bottled or pipe water in dwelling or premises          |  |

15 Does your house have electricity?

|        |                          |
|--------|--------------------------|
| 1. No  |  |
| 2. Yes |  |

## Part 2 Adolescents oral health knowledge and behaviors

16. I can avoid tooth decay by accomplishing the following;

- |                                                                                                                                              | 1=yes                    | 2=no                     |
|----------------------------------------------------------------------------------------------------------------------------------------------|--------------------------|--------------------------|
| 1. Restricting eating of sugar containing foods such as vitumbua, filters, cake, chocolate to less than five times per day                   |  |  |
| 2 Restricting drinking of sugar sweetened drinks such as tea, coffee, porridge, coke, fanta, mukoyo or juice to less than five times per day |  |  |
| 3. Using fluoride toothpaste to brush my teeth at least twice a day spitting the foam but not rinsing it out                                 |  |  |
| 4 Visiting a dentist at least once a year for dental check up                                                                                |  |  |

17. I can avoid bleeding gums by fulfilling the following;

- |                                                                                                 | 1=yes                    | 2=no                     |
|-------------------------------------------------------------------------------------------------|--------------------------|--------------------------|
| 1. Restricting eating/drinking of sugar containing foods/ drinksto less than five times per day |  |  |
| 2. Brushing teeth for 2 minutes at least twice a day                                            |  |  |
| 3. Visiting a dentist at least once a year for dental check up                                  |  |  |
| 4 Using a dental floss to clean between my teeth                                                |  |  |
| 5 Using a tooth pick to clean between my teeth                                                  |  |  |

18. When should a tooth brush be changed

- |                                                  | 1=yes                    | 2=no                     |
|--------------------------------------------------|--------------------------|--------------------------|
| 1. When the brush head is broken                 |  |  |
| 2. Once a month                                  |  |  |
| 3. Three months or when bristlesflare out (bend) |  |  |
| 4 I don't know                                   |  |  |

19. During the past 30 days how often did you drink sugar sweetened drinks such tea, coffee, porridge, coke, fanta, mukoyo or juice?

- |                                |                          |
|--------------------------------|--------------------------|
| 1. I didn't                    |  |
| 2. Occasionally per week       |  |
| 3. Once per day                |  |
| 4. Twice to four times per day |  |
| 5. Five times or more per day  |  |

20. During the past 30 days how often did you eat sugar containing foods such vitumbua, filters, cake, chocolate?

- |                                |                          |
|--------------------------------|--------------------------|
| 1. I didn't                    |  |
| 2. Occasionally per week       |  |
| 3. Once per day                |  |
| 4. Twice to four times per day |  |
| 5. Five times or more per day  |  |

21. How many times in a day did you brush your teeth in the past 30 days?

- |                                  |                          |
|----------------------------------|--------------------------|
| 1. I didn't brush at all         |  |
| 2. I brushed but not everyday    |  |
| 3. I brushed once a day          |  |
| 4. I brushed twice or more a day |  |

22. What do you use to clean your teeth?

- |                        |                          |
|------------------------|--------------------------|
| 1. Nothing             |  |
| 2. Finger              |  |
| 3. Chewing stick       |  |
| 4. Plastic tooth brush |  |

23. If you use a plastic tooth brush how often do you change it?

- |                                  |                          |
|----------------------------------|--------------------------|
| 1. After 1 month                 |  |
| 2. After 2 months                |  |
| 3. After 3 months                |  |
| 4. When worn out (bristles bent) |  |

24. Do you use toothpastes for tooth brushing?

- |        |                          |
|--------|--------------------------|
| 1. No  |  |
| 2. Yes |  |

25. If you do, does the tooth paste contain fluoride

- |                 |                          |
|-----------------|--------------------------|
| 1. No           |  |
| 2. Yes          |  |
| 3. I don't know |                          |

26. How often did you use fluoridated toothpaste during the past 30 days?

- |                               |                          |
|-------------------------------|--------------------------|
| 1. I didn't use tooth paste   |  |
| 2. I used but not everyday    |  |
| 3. I used once a day          |  |
| 4. I used twice a day or more |  |

27. How many times did you attend for dental checkup in past 1 year?

1. I did not attend
2. I attended once
3. I attended twice or more

|  |
|--|
|  |
|  |
|  |

28. If you did not attend for check up, what is the reason?

1. I did not have any problem
2. My parents didn't have money
3. My parents didn't have time
4. The clinic is very far
5. I had fear of a dentist
6. I used traditional medicine
7. Others Specify .....

|  |
|--|
|  |
|  |
|  |
|  |
|  |
|  |

29. Did you experience any of the following dental problems in the past 3 months?

- |                          | 1=yes                    | 2=no                     |
|--------------------------|--------------------------|--------------------------|
| 1. Painful tooth         |  |  |
| 2. Painful gums          |  |  |
| 3. Swollen gums          |  |  |
| 4. Bleeding gums         |  |  |
| 5. Injury to teeth       |  |  |
| 6. Bad teeth arrangement |  |  |
| 7. Others Specify .....  |                          |                          |

30. How would you describe the health of your teeth?

1. Very poor
2. Poor
3. Good
4. Very good

|  |
|--|
|  |
|  |
|  |
|  |

31. How would you describe the health of your gums?

1. Very poor
2. Poor
3. Good
4. Very good

|  |
|--|
|  |
|  |
|  |
|  |

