#### **4.10. Study outcomes**

The expected primary outcomes are improved oral health (dental caries status and gingivitis) and OHRQoL. The secondary outcomes include improved oral hygiene (plaque score) and oral health knowledge and related behaviors. The effect sizes for improvement in oral health and oral health related quality of life are based on average improvement achieved in similar studies reviewed.

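### Appendix 1, Part 2 shows pupils the recommended practices and their thresholds just before asking about their own behaviour at the same thresholds, which risks cued self-report

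*Protocol*

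**What the plan says.** Part 2 of the questionnaire in Appendix 1 opens with three knowledge questions (16 to 18) and then asks about the pupil's own habits.

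Question 16, "16. I can avoid tooth decay by accomplishing the following", is a yes/no list of four practices, all of them advice. Two examples are "Restricting eating of sugar containing foods such as vitumbua, filters, cake, chocolate to less than five times per day" and "Using fluoride toothpaste to brush my teeth at least twice a day spitting the foam but not rinsing it out".

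The behaviour questions follow. The highest answer for sugary drinks (question 19) and sugary foods (question 20) is "5. Five times or more per day". Question 21 asks "How many times in a day did you brush your teeth in the past 30 days", and its top answer is "4. I brushed twice or more a day". Question 27 asks "How many times did you attend for dental checkup in past 1 year".

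Section 4.10 gives these answers their status: "The secondary outcomes include improved oral hygiene (plaque score) and oral health knowledge and related behaviors". Knowledge and behaviours are also the subject of specific objective 3 (section 2.2). Section 4.9.1 describes one self-administered questionnaire, with data collected at baseline and at 6, 12, 18 and 24 months. Section 4.9.2 states that participants cannot be blinded.

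**The concern.** A pupil aged 10 to 14 reads that keeping certain named foods below five times a day prevents decay, and a few lines later reports how often he or she eats those same foods. The form has by then indicated which answer is desirable. Some pupils who do not follow the advice may report that they do.

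Two things are at stake. The reported levels of good behaviour, which section 4.12 plans to tabulate and to use in cross-tabulations, may be too high. The between-arm contrast in behaviour under objective 3 may also be distorted, because it rests on these answers alone. No item measures the cue, so the analysis cannot remove it afterwards.

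The control arm receives no oral health education until the end of follow-up (Table 1), yet this form shows it the core of the taught advice at each visit.

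**Working it through.** **Plan's own figure.** The protocol gives no expected level or effect for behaviour, so there is none to reproduce. Its only calculation concerns mean DMFT (section 4.4): 4 × (1.96 + 1.03)² × 1.34² / 0.268² = 894; 894 × [1 + 79 × 0.01] = 1600; 1600 × 1.10 = 1760. The arithmetic reproduces but has no bearing on this point.

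**Step 1: compare the items (Appendix 1, Part 2).**

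| Practice | Shown in the knowledge block | Asked as behaviour | Shared cut |
|---|---|---|---|
| Sugary foods | 16.1 | 20 | five a day; same food examples |
| Sugary drinks | 16.2 | 19 | five a day; same drink examples |
| Brushing, fluoride paste | 16.3, 17.2 | 21, 26 | two a day |
| Dental check-up | 16.4, 17.3 | 27 | one a year |
| Changing the brush | 18.3 | 23 | three months |

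The first four rows are behaviours that section 4.11.2 lists as dependent variables. Brush replacement is not on that list, so the last row matters less. The same limits on sugar, brushing, brush replacement and check-ups appear in the peer messages of section 4.6.

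**Step 2: how far the knowledge block reveals the answer.** Question 16 has no evident distractor. Question 17 includes a tooth pick. Question 18 includes monthly replacement, a broken head and a don't-know option. The cue is therefore strongest from question 16 and only partial from 17 and 18.

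**Step 3: effect of a cue.** Let p be true adherence and c the share of non-adherent pupils who report adherence because of the cue. Then reported adherence = p + c(1 − p). All values of p and c below are assumptions.

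*Equal cue in both arms.* The risk difference is multiplied by (1 − c).

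- True 50% control and 65% intervention: OR = (0.65/0.35)/(0.50/0.50) = 1.86. With c = 0.10, reported 0.50 + 0.10 × 0.50 = 0.550 and 0.65 + 0.10 × 0.35 = 0.685. OR = (0.685/0.315)/(0.550/0.450) = 1.78. The difference falls from 15.0 to 13.5 points.
- True 60% and 75% (OR 2.00): c = 0.1, 0.2, 0.3 and 0.5 gives OR 1.94, 1.88, 1.83 and 1.75, with differences of 13.5, 12.0, 10.5 and 7.5 points.
- No true effect (60% in both arms): OR stays 1.00 for any equal c.

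*Unequal cue.* With true 60% and 75%:

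- c = 0.2 in control and 0.1 in intervention gives 0.680 and 0.775, OR 1.62.
- c = 0.1 in control and 0.2 in intervention gives 0.640 and 0.800, OR 2.25.
- With no true effect (60% in both arms), the same two cases give OR 0.84 and 1.20.

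An equal cue can only dilute. Bias away from the null, or a false effect, needs cueing that differs between arms.

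**The case against.** The strongest reply is that this is a possible risk, not an error. The documents hold no data on order effects. Both arms complete the same form, and an equal cue costs little. Questions 16 to 18 are yes/no items, two of the three contain alternatives, and question 27 comes well after the block. Section 4.11.3 says the questions come from standardized instruments used in the region, and the activity plan schedules pretesting. Knowledge is itself a secondary outcome, so asking behaviour first might prime the knowledge answers. Much of any arm-specific over-reporting would come from unblinded self-report, which no question order removes.

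Most of this stands as a limit on the claim. It does not remove the point. Question 16 has no evident distractor and reuses the wording of the behaviour items. Whether the order comes from the source instruments cannot be checked from the protocol. Reverse priming should be weaker, because questions 19 to 28 never say which answer is recommended. The mitigation in section 4.14 for pupils changing their conduct under observation is that the intervention stops six months before the last follow-up. That does not touch a cue printed on the form, which recurs at 24 months.

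A reader might go further and infer that the behaviour effect is biased, or that cueing confined to controls would cut an OR of 1.86 to 1.52 (10% cue: 0.55 against 0.65) or 1.24 (20% cue: 0.60 against 0.65). The documents do not support this. Control-only cueing assumes no cue at all among pupils who hear the same messages every two weeks, and nothing in the protocol indicates which arm would respond more.

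**Conclusion.** The point holds as a risk of cued self-report in a secondary outcome, and it is minor. It would overstate good behaviour. If cueing is similar in both arms, it dilutes the between-arm difference modestly: from OR 1.86 to 1.78 at an assumed 10% cue, and from 2.00 to between 1.94 and 1.75 over an assumed range of 10% to 50%. If cueing differs by arm, size and direction are unknown. The order and the matching cut-points are facts of Appendix 1; the adherence levels and cue sizes are assumptions. The clinical outcomes (caries, gingival bleeding, plaque) are not affected. There is no contradiction or numerical error in the protocol here.

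**What to change.** In Appendix 1, Part 2, place questions 19 to 28 before questions 16 to 18, leave the wording unchanged, and use this order at baseline and every follow-up. The ten behaviour items become 16 to 25 and the three knowledge items 26 to 28; question 29 onward keeps its number.

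The cost is renumbering before printing, with no added items or time. Three downsides remain. The behaviour items may slightly prime the knowledge items. Pupils will still have seen the knowledge block at earlier visits. Bias from unblinded self-report is untouched.

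If baseline was already collected in the present order, keep that order so that each pupil's paired answers stay comparable, and add cued self-report of behaviour to the limitations in section 4.14.
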